#### Inhibition training task

The intervention is an online GNG training task as developed by Lawrence et al. [36], modified to incorporate images of smoking. The task included nine smoking images (or household items in the control group), nine relaxation images (or household items in the control group) and 18 neutral filler images presented on the left or right of the computer screen (see Fig. 1). Each image was presented for 1250 ms followed by a 1250 ms inter-stimulus interval. Participants were instructed to indicate whether the image is located to the left or the right of the screen using the keys “C” and “M” respectively on their keyboard. On half of the trials, the frame around the picture was bolded and the participants were required to not respond (no-go trials). On the other half of the trials the frame was not bolded (go trials) and the participant were required to respond as quickly as possible. During each training session participants completed 6 training blocks, with each of the 36 images presented once per block. At the end of each block, participants were provided with feedback on their accuracy and mean correct go reaction time and will be encouraged to continue trying to beat their own score. Each training session will last for approximately 10 min. Participants were asked to complete the training at home in a quiet place and preferably, when they experienced cravings for a cigarette.

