#### Intervention group

The intervention consisted of nine smoking-related images, nine relaxing images.

(i.e. depicting relaxing/enjoyable activities), and 18 neutral filler pictures (e.g. clothing). For the intervention group, the smoking-related pictures were always “no-go” trials and the non-smoking pictures were always “go” trials. The neutral pictures were equally “go” and “no-go” trials (see Fig. 1). The neutral filler pictures were incorporated to prevent participants from easily identifying the associative rules of the task and to ensure the task remains challenging and engaging.

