The primary and secondary hypotheses will be analysed using separate mixed-design ANOVAs and a Chi-square analysis for the binary outcome. Depending on the rate of smoking abstinence at follow up the outcome variable will be calculated as either binary (smoking abstinence: yes/no) or percent days abstinence if Chi-square analysis is contraindicated due to low numbers in each cell. For all other mixed design ANOVAs group (i.e., intervention or control) will be included as the between-subjects factor and time (survey time points) is the within-subjects factor. For the smoking reduction primary hypothesis, the repeated-measures factor will be the average number of cigarettes smoked per day at each timepoint (i.e., baseline, post-intervention, 1 month and 3 months post intervention). For the secondary hypotheses, the repeated-measures factor will be craving or nicotine dependence at each timepoint. The predictor hypotheses will be examined using separate moderated regression analyses, with group as the predictor variable, impulsivity and dose as the moderator variable and change in smoking as the dependent variable.

The two mediation hypotheses will be analysed utilising a linear mixed model approach to examine whether the effects of INST training on level of smoking will be mediated by devaluation of smoking stimuli or an independent measure of response inhibition (SSRT).

The exploratory questions related to self-confidence and motivation will be examined using a separate mixed-design ANOVA, with group included as the between subjects factor and self-confidence and motivation at each timepoint included as the repeated-measures factor.

Repeated measures ANOVAs will be performed on “go” reaction times and “no-go” accuracy to examine stimulus-specific learning effects (100% stimuli vs. 50% stimuli) over time (first vs. fourth training session as per the analysis by Lawrence and colleagues to allow comparability). Evidence of learning across the two time points will be indicated by faster reaction time on 100% go stimuli and fewer errors on 100% no-go stimuli. Any further exploratory analyses will be labelled as such in the publication.

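### The stated evidence of stimulus-specific learning names only the 100% images and does not require a larger gain than on the 50% images, so ordinary practice could be reported as learning

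*Protocol article*

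**What the plan says.** The last paragraph of the Analysis plan schedules repeated measures ANOVAs on go reaction time and no-go accuracy "to examine stimulus-specific learning effects (100% stimuli vs. 50% stimuli) over time". The two occasions are "first vs. fourth training session". The next sentence says what will count: "Evidence of learning across the two time points will be indicated by faster reaction time on 100% go stimuli and fewer errors on 100% no-go" images.

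Three other sections bear on how that rule behaves:

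- **Intervention group:** the pairing rule is that "the smoking-related pictures were always “no-go” trials and the non-smoking pictures were always “go” trials. The neutral pictures were equally “go” and “no-go” trials". The always-go pictures are the nine relaxing scenes.
- **Control group:** the household pictures appear as go and no-go in equal measure, so this arm has no 100% images.
- **Inhibition training task:** when a block ends, "participants were provided with feedback on their accuracy and mean correct go reaction time and will be encouraged to continue trying to beat their own" previous result.

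**The concern.** The question posed is whether the fixed pairings are learned over and above getting better at the task. The matching null hypothesis is that 100% images improve no more between sessions 1 and 4 than 50% images do. The sentence that defines the evidence refers only to the 100% images, and it can be taken in two ways that do not test this null.

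- **As change over time on the 100% images.** This is the literal reading, since the sentence speaks of the two time points. Anyone who becomes quicker and more accurate at the task satisfies it.
- **As an overall difference between 100% and 50% images.** Contingency and picture content coincide in the INST arm, so a fixed difference in how fast people respond to relaxing and neutral pictures satisfies the reaction-time half. The same holds for errors on smoking and neutral pictures.

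This is the only planned analysis of learning within the training task itself. If the rule is followed as written, the report could say that participants acquired stimulus-specific associations when only general improvement was shown.

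**Working it through.** The document gives no figure to reproduce here, so the check is of which contrast answers the question, followed by an illustration of size.

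**Trials available per session** (Inhibition training task; Intervention group): 6 blocks x 36 images = 216.
- 100% go: 9 x 6 = 54. 100% no-go: 9 x 6 = 54.
- 50% images: 18 x 6 / 2 = 54 go and 54 no-go.

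The comparator is therefore as well measured as the 100% images.

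**What each contrast estimates.** For go reaction time, let μ be the session 1 mean on 50% images and p the practice gain common to all images. Let c be the amount by which 100% images are already faster in session 1, through content or through learning within that session. Let L be the extra gain on 100% images between sessions.

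| | Session 1 | Session 4 |
|---|---|---|
| 100% go | μ − c | μ − c − p − L |
| 50% go | μ | μ − p |

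- (a) Gain on 100% images alone: p + L. Positive under practice even if L = 0.
- (b) Overall 50% minus 100% difference: c + L/2. Positive under a content effect even if L = 0.
- (c) Interaction: (p + L) − p = L. Zero if L = 0.

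If practice differs by content (p100 and p50), (c) becomes L + (p100 − p50). No arm shows the same pictures at 50%, so the design cannot separate these two terms.

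**Illustration, reaction time only.** Assumed, not in the document: SD 25 ms per person and cell; practice 10 or 20 ms; fixed content difference 10 ms; 35, 46 or 75 INST participants. There were 4,000 runs with L = 0, using paired t tests at two-sided .05 and counting only results in the direction of learning (nominal 2.5%).

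Standard errors at n = 46:
- (a) 25√2/√46 = 5.21 ms, so a 10 ms practice gain gives 10/5.21 = 1.92 against a critical value of 2.01.
- (b) 25/√46 = 3.69 ms, so a 10 ms content difference gives 10/3.69 = 2.71.
- (c) 50/√46 = 7.37 ms, with expectation zero.

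| False learning | n = 35 | n = 46 | n = 75 |
|---|---|---|---|
| (a), practice 10 ms | 37% | 47% | 67% |
| (a), practice 20 ms | 91% | 96% | 99.8% |
| (b), content 10 ms | 63% | 77% | 92% |
| (c), all no-learning settings | 2.1–2.9% | 2.2–2.8% | 2.4–3.0% |

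With a true L of 15 ms (practice 20 ms, content 10 ms), (c) is significant in 41%, 51% and 73% of runs, while (a) is significant in all of them.

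**Illustration, both parts of the rule.** The sentence joins reaction time and errors, so the rates for (a) overstate it. A second simulation (2,000 runs per setting) took 52 INST participants reaching session 4: 75 x 0.70 = 52.5, using the Power analysis figure of up to 30% not completing four sessions. It assumed a trial-level reaction-time SD of 110 ms, a between-person SD of 50 ms in session change, and errors binomial out of 54 with logit-scale SDs of 0.6 (person) and 0.3 (session). Practice was equal on 100% and 50% images.

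| Practice assumed | Both parts met on 100% images |
|---|---|
| 10 ms; errors 5% to 4% | 9.5% |
| 20 ms; errors 5% to 3.5% | 54.3% |
| 30 ms; errors 6% to 3.5% | 94.3% |

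**The case against.** The best defence is that the two sentences belong together. The ANOVA has stimulus type and session as within-subject factors, so it yields the interaction, and the second sentence may merely give the expected direction. A reader might infer from the rule that the plan leaves out the 50% images. It does not: they are in the analysis as comparator, and nothing rules out using the interaction. What remains is that such an ANOVA gives two main effects and an interaction, and the one sentence saying which result counts does not pick the interaction.

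A second defence is that a journal article condenses, and the decisive ANOVA term is usually left to a fuller plan. That would answer a missing detail. Here a rule is stated, and taken literally it does not match the question in the sentence before it.

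Third, the level-difference reading fits poorly with a sentence about two time points, and a fixed content effect cancels in any change over time. This stands. Content is the lesser of the two problems, and the rates for contrast (b) belong to the less natural reading. They also assume the same picture effect in everyone; variation between people would lower them.

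Fourth, a reader might infer that a false positive here would distort the trial's main conclusion, for example by presenting a null smoking result as training that was learned but did not work. The document does not support that. The check is not among the primary, secondary, moderator or mediator hypotheses. The mediators are tested separately, through stimulus ratings and stop signal reaction time, and no section makes another analysis depend on this one.

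**Conclusion.** The point holds as a minor fault in a stated decision rule. The planned comparison is sound, but the criterion attached to it can be met by general practice and does not require the larger gain on 100% images that stimulus-specific learning implies.

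The direction follows from the algebra. The size does not: the percentages rest on assumed practice gains, picture effects and variances, and the range from 9.5% to 94.3% for the two-part rule shows how strongly they depend on them. They are illustrations, not estimates for this trial.

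The interaction is the better criterion but not a complete one. It removes practice common to all images and any constant content difference. It does not remove practice that proceeds at different rates on smoking, relaxing and neutral pictures.

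**What to change.** Replace the criterion sentence with wording such as:

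> Stimulus-specific learning across the two sessions will be judged by the stimulus type (100% vs 50%) x session interaction in the INST arm: a larger fall in reaction time for 100% go than for 50% go images, and a larger fall in errors for 100% no-go than for 50% no-go images. Change on the 100% images alone will be reported as possibly general practice. An overall 100% vs 50% difference will be reported as confounded with picture content, although it could also reflect learning within session 1. Practice rates that differ by picture content would also produce the interaction, because no arm shows the same pictures at 50%.

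The cost is a few lines of text. No new data, task change or additional model is needed. The small downside is that a positive learning result becomes somewhat harder to obtain, because the interaction contrast has a larger standard error than the simple gain.

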#### Power analysis

As previous ICT studies have not targeted abstinence the current study was powered on smoking reduction based on Lawrence et al., [36] weight reduction ICT outcome data. Power analysis conducted via G*power indicated that an overall sample size of 92 is required to detect a medium effect size (approximately .50 cohen’s d based on Lawrence et al.) at the .05 alpha level using linear techniques (power = .80). Given that it is expected that approximately 25% will be lost to follow-up and up to 30% would not complete a minimum of 4 sessions, the target of the current study was set at 150 at the time of trial registration. However, estimated target sample may be amended if attrition is better than expected.

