**Methods/design:**

This randomised controlled trial will recruit nicotine dependent smokers aged between 18 and 60 using social media and advertisements in Victoria, Australia. The sample target was 150 to account for drop out and non-adherence. Once informed consent has been obtained, participants complete a range of baseline measures during a face to face interview. Participants are randomly allocated to one of two online training conditions: an intervention training group (INST), which requires participants to exercise response inhibition towards smoking-related stimuli; or an active control group, which requires participants to exercise response inhibition towards household items and does not include any smoking-related stimuli. They complete the first training session during the interview to ensure the training protocol is clear. Both groups are instructed to complete a further 13 training sessions (1 per day) at home on their computer and follow-up phone calls will be conducted at three time points: post-intervention, one-month and three months. The primary outcomes are: a) rates of smoking cessation and; b) reduction in the quantity of average daily smoking at post-intervention, one and three months follow-up.

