### Analysis plan

All participants will be included in the intent-to-treat analyses for the primary and secondary hypotheses. If relevant, per protocol analysis will include those who complete at least four sessions of the training (as per Lawrence et al. [36]) and achieve a training accuracy of at least 70%. SST data will be included for those who yield an accuracy of 40–60% on stop trials and at least 70% on go trials. Prior to analyses, all variables will be examined through IBM Statistical Package for Social Sciences (SPSS Version 25) for accuracy of data entry, missing values and fit between their distributions and the assumptions of multivariate analysis. Any violations will be addressed as per standard protocols [64].

Missing data will be managed using SPSS. First, a missing value analysis will be conducted to determine the percentage and pattern of missing data. If missing data are found to relate to a measured participant variable, those variables will be included as covariates in the analyses. If appropriate, multiple imputation will be used to replace missing values and the imputation model will include baseline covariates and outcome data. Missing data will be imputed using the Markov Chain Monte Carlo method or the Monotone method, contingent upon the pattern of missing data. A minimum of five imputed datasets will be produced [65]; however, depending on the percentage of missing data, a minimum of 20 imputed datasets may be required [66]. Wherever possible, results from the complete case analysis will be compared with results based on imputed data. If there are important differences, explanations will be offered.

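### The target of 150 appears to multiply 92 by (1 + loss) instead of dividing by the retained fraction, and it deducts non-completers whom the intent-to-treat analysis keeps

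*Protocol article*

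**What the plan says.** The Power analysis section states that "an overall sample size of 92 is required" for a Cohen's d of about 0.50, alpha 0.05 and power 0.80. It then expects that "approximately 25% will be lost to follow-up and up to 30% would not complete a minimum of 4 sessions", and on that ground "the target of the current study was set at 150 at the time of trial registration". The arithmetic from 92 to 150 is not shown, nor is the overlap between the two losses. The abstract gives the same purpose: "The sample target was 150 to account for drop out and non-adherence". The Power analysis section closes by allowing that the "estimated target sample may be amended if attrition is better than expected".

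The Analysis plan fixes the analysis sets. For the main comparisons, "All participants will be included in the intent-to-treat analyses for the primary and secondary hypotheses". The four-session minimum appears there only as part of the definition of a per-protocol set, to be used if relevant, together with a training accuracy of at least 70%.

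**The concern.** Two things do not fit together.

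First, to end with 92 after losses, 92 has to be divided by the proportion expected to remain. Multiplying by one plus the loss always gives too small a target, and the gap grows with the size of the loss. Losses of 25% and 30% are large enough for it to matter.

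Second, the target counts people with fewer than four sessions as lost, but the primary analysis keeps them. In an intent-to-treat comparison they do not reduce the head count; they pull the average effect towards zero. The protocol's own dose hypothesis (better outcomes with more sessions) points the same way. Adding heads for non-completion does not show what power remains for a diluted effect.

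At stake is whether 150 delivers the stated 80% power, and for which analysis set. The same calculation would also be the reference point if the target were lowered under the attrition sentence.

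**Working it through.** **Inputs.** From the Power analysis section: required number 92, loss to follow-up 25%, non-completion up to 30% (taken at its upper limit), target 150, d = 0.50, alpha 0.05, power 0.80. Assumed because not stated: the overlap of the two losses, and a two-sided test. Equal allocation is inferred from the balanced blocks under Randomisation.

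**Step 1: reproduce the plan's figure.** 92 × 1.25 = 115; 115 × 1.30 = 149.5, rounded up to 150. The additive version, 92 × 1.55 = 142.6, does not match. Nor does dividing by the retained fraction under any of the simple readings in Step 2.

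**Step 2: divide by the retained fraction.**

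| Which losses count | Combined loss | Target needed to keep 92 | Left from 150 |
|---|---|---|---|
| Follow-up loss only (intent-to-treat) | 25% | 92/0.75 = 122.7 → 123 | 112.5 → 112 |
| Both, full overlap | 30% | 92/0.70 = 131.4 → 132 | 105 |
| Both, independent | 1 − 0.75 × 0.70 = 47.5% | 92/0.525 = 175.2 → 176 | 78.75 → 79 |
| Both, no overlap | 55% | 92/0.45 = 204.4 → 205 | 67.5 → 67 |

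**Step 3: the break-even.** 150 leaves 92 when the combined loss is 1 − 92/150 = 38.7%. That requires 25 + 30 − 38.7 = 16.3 percentage points of participants to be in both groups, so about 0.163/0.25 = 65% of those lost to follow-up must also be non-completers. Independence gives 0.25 × 0.30 = 7.5 points.

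**Step 4: illustrative power at the numbers left.** Two-sided unadjusted two-sample t-test, alpha 0.05, d = 0.50:

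- intent-to-treat with follow-up, N = 112: 0.75
- completers with follow-up under independence, N = 79: 0.59

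With adjustment for baseline, d is divided by √(1 − r²). At an assumed correlation r of 0.5 to 0.6, power is 0.86 to 0.91 at N = 112 and 0.72 to 0.78 at N = 79. The protocol states no correlation.

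**Step 5: dilution, as a sensitivity case.** If 30% of those analysed gain nothing and the rest gain 0.50, the average effect is 0.70 × 0.50 = 0.35. The unadjusted t-test at N = 112 then has power 0.45. The zero-benefit assumption is not in the protocol.

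**The case against.** A reader might infer that 150 has no basis in the stated inputs. The documents do not support that: 92 × 1.25 × 1.30 gives it. The error is in the form of the inflation.

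A reader might also infer that the primary analysis falls short of the plan's own requirement. It does not: after 25% loss about 112 remain against 92. Counting non-completers made the target larger, which is conservative for the intent-to-treat head count, and sizing a trial so that a per-protocol set is also adequate is a legitimate choice. What stands against this is that the protocol does not say 150 was chosen for that set.

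Overlap is a fair defence. People who stop online training may well be the same people who are later lost, and 30% is given as an upper limit. The figure of 150 lies inside the range 132 to 205, so heavy overlap would rescue it. The protocol does not claim such overlap, and multiplying two separate factors treats the losses as separate.

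It is tempting to conclude that neither analysis set has 80% power. That is not shown. The figures 0.75, 0.59 and 0.45 come from an unadjusted t-test, whereas the Analysis plan specifies mixed-design ANOVA over four time points including baseline, and the baseline-adjusted figures at N = 112 exceed 0.80. The 0.45 is also an extreme: every participant completes the first session at the baseline interview, and it assumes that 0.50 is an effect under full adherence. How 92 was derived is a separate matter; it is taken as given here.

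Finally, the attrition sentence does not by itself cost power. Lowering the target when losses are smaller can keep the same evaluable number. The weakness is that the sentence names no floor and rests on a faulty calculation.

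**Conclusion.** The concern holds in a limited form. The target of 150 appears to come from multiplying by (1 + loss). Correct inflation of 92 for both losses gives 176 under independence (132 to 205 across the possible overlaps), and 150 leaves about 79 completers with follow-up (105 to 67). The shortfall against 92 therefore depends on overlap and disappears if the combined loss is 38.7% or less. It concerns only the optional per-protocol set, whose 70% accuracy rule could reduce the number further.

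For the intent-to-treat analysis, the 30% deduction is of the wrong kind. The head count of about 112 is adequate against 92, but the effect of non-completion on the size of the difference is not addressed. Whether power there is above or below 0.80 cannot be settled from the document, because neither the test behind the calculation nor a baseline correlation is given. The inflation arithmetic and the mismatch with the analysis set rest on stated figures; the power values are illustrations under named assumptions.

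**What to change.** Rewrite the Power analysis section, without changing the recruitment target:

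- State that 150 randomised gives about 112 with follow-up for intent-to-treat (25% loss) and about 79 for the per-protocol set if the losses are independent. State the overlap assumed and which set the target is meant to serve.
- Remove the 30% non-completion deduction from the intent-to-treat calculation.
- Restate power for each set, naming the test and any assumed baseline correlation. For example, for d = 0.50 with a two-sided unadjusted t-test: 0.75 at 112 and 0.59 at 79, with the baseline-adjusted figures alongside if that is the planned analysis.
- Add a diluted-effect figure for intent-to-treat as a sensitivity case, labelled as an assumption.
- Tie any lowering of the target for better attrition to the corrected requirement (the required number divided by the retained fraction), or delete that sentence.

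The cost is wording only. No participants are added, but the stated figures become less favourable.

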#### Randomisation

Immediately following the completion of the baseline assessment, participants began the online training task. Participants were automatically randomised to either the intervention or the control training task via a pre-computed randomisation procedure. A permuted block randomisation procedure was utilised [46] whereby participants were allocated to the intervention or control group through the use of a randomly generated number. The permuted blocks were organised in groups of ten, the details of which were not known by investigators involved with the administration of the trial. The use of the permuted block randomisation process ensures that intervention group numbers will be balanced at the end of each block and is thus the recommended process in studies with smaller samples.

Upon finishing this task participants were instructed to complete the online training task once per day for the next 13 days, totalling 14 sessions. They were asked to rate their smoking craving level before and after each training session. Twice per week, participants were sent text reminders to complete the training. All data from the online training task and outcome measures were securely stored on the Deakin University server and linked to an anonymous participant ID number such that only de-identified data were available to researchers. The data was checked for training task performance accuracy and participant adherence to the training protocol by a research assistant who was independent from investigators and not involved in data collection or analyses.

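### The target of 150 may be amended if attrition is low, with 92 the only benchmark; on the stated inputs 92 analysed gives about 66% power unless an unstated assumption is added

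*Protocol article*

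**What the plan says.** The Power analysis section bases the sample size on smoking reduction. It states that "an overall sample size of 92 is required to detect a medium effect size", put at roughly .50 in Cohen's d, "at the .05 alpha level using linear techniques (power = .80"). It expects that "approximately 25% will be lost to follow-up" and that up to 30% will not complete four sessions, and on that basis sets the target at 150. The Abstract gives the same purpose: "The sample target was 150 to account for drop out and non-adherence".

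The Power analysis section then closes with "However, estimated target sample may be amended if attrition is better than expected". It gives no replacement target, no threshold for what counts as better, and no minimum number of analysed participants. No matching provision is made for attrition worse than expected.

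The Analysis plan puts all participants in the intent-to-treat analysis of the primary hypotheses. Completing four sessions matters only for the per-protocol set. Smoking reduction is to be tested with a mixed-design ANOVA over four time points including baseline.

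**The concern.** The closing sentence has meaning only as permission to recruit fewer people. A trial team using it needs a figure to cut towards, and the section offers one: 92. If 92 is too small for the effect and power stated beside it, good retention would be spent on a smaller trial when it could have brought the trial up to its stated power. At stake is the power of the primary outcome on which the trial was sized.

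**Working it through.** **Inputs.** From the Power analysis section: d = .50, alpha = .05, power = .80, stated requirement 92, target 150, loss to follow-up 25%, non-completion up to 30%. From the Randomisation section: two groups balanced within blocks, so 1:1. Sidedness is not stated; two-sided is assumed and one-sided is also shown.

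**1. Can 92 be reproduced?** For an unadjusted comparison of two means, the normal approximation per group is 2(1.960 + 0.842)² / 0.50² = 62.8, so 63 per group and 126 in total. The exact noncentral t gives 128 two-sided and 102 one-sided. Neither is 92. Three routes do reach 92 or come close:

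- A multiple-regression overall F test with f² = 0.15 and five predictors gives exactly 92. But d = .50 corresponds to f² = 0.25² = 0.0625, and testing one predictor at that size again needs 128.
- A baseline-adjusted comparison needs 128 × (1 − ρ²). This equals 92 at ρ = √(1 − 92/128) = 0.53.
- The between-groups effect in a repeated-measures ANOVA (f = 0.25, four measurements) needs 82, 90 or 100 at a correlation of 0.5, 0.6 or 0.7.

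The article states neither the f² nor either correlation.

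**2. Can 150 be reproduced?** Yes: 92 × 1.25 × 1.30 = 149.5. To leave 92 after both losses, one divides: 92 / (0.75 × 0.70) = 175.2, so 176. With both planned losses stacked, 150 leaves 150 × 0.75 × 0.70 = 79. With the 25% loss alone, 150 leaves 112.

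**3. Power at each analysed size.** The noncentrality parameter is d√N / 2, with N − 2 degrees of freedom and two-sided .05. At N = 92 it is 0.50 × √92 / 2 = 2.40, which gives 66.0% (76.9% one-sided). At N = 112 power is 74.6%, at 128 it is 80.1%, and at 150 it is 86.0%.

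**4. Keeping 150 against cutting to 92 analysed**, for losses below the expected 25%:

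| Loss | Analysed from 150 | Power | Recruits that leave 92 | Power at 92 | Points given up |
|---|---|---|---|---|---|
| 0% | 150 | 86.0% | 92 | 66.0% | 20.0 |
| 5% | 142.5 | 84.2% | 97 | 66.0% | 18.2 |
| 10% | 135 | 82.2% | 103 | 66.0% | 16.2 |
| 15% | 127.5 | 80.0% | 109 | 66.0% | 14.0 |
| 20% | 120 | 77.5% | 115 | 66.0% | 11.5 |

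On this test, 150 reaches 80% only while loss is at most 1 − 128/150 = 14.7%.

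**5. What a floor of 128 would allow.** At 10% loss, 128 / 0.90 = 142.2, so 143 recruits. At 15% loss, 128 / 0.85 = 150.6, so 151, and no reduction is possible.

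**The case against.** The strongest reply is that the sentence is consistent with the article's own figures. If 92 is right and the primary analysis is intent-to-treat, only the 25% loss counts. Then 150 leaves 112, there is slack at the expected attrition, and trimming recruitment when retention is better is ordinary practice. Nor is the planned analysis an unadjusted t test at one visit. It uses baseline and three later measurements, and a baseline-adjusted comparison with 92 would have 78% power at a correlation of 0.5, 80% at 0.53 and 84% at 0.6. A one-sided test would make 112 adequate (84%), although 92 would still give only 77%.

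This reply stands as far as it goes. It makes the point conditional on 92 being too small for d = .50. It does not establish that 92 is adequate, because the article states none of the assumptions that would make it so.

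A reader might go further and infer that low attrition is the only case in which 150 attains its power, and that the rule throws that case away. The documents do not support this. The first half fails if 92 is accepted. The second fails because the wording is permissive and names no new target: a reduction that kept 128 analysed would also comply. Better than expected also covers losses between 15% and 25%, where 150 itself falls below 80% on the two-sided test.

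A reader might also infer that the decision would rest on an early attrition figure or be taken with sight of outcomes. The article gives no timing and names attrition as the only trigger. Such operational detail may sit in the full protocol, so no criticism is made of it. Finally, the Design section reports no protocol amendments after the trial began, and nothing shows that the option was used.

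**Conclusion.** The point holds in conditional form. The article permits the target to be amended under good retention, offers 92 as the only benchmark, and sets no floor on the number analysed. On the stated inputs with an unadjusted two-sided test, a trial cut to 92 analysed would have about 66% power against the stated .80. At 10% loss that is about 16 points less than keeping 150 would give.

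The assumptions are d = .50, equal arms, two-sided .05, one time point, no gain from correlation with baseline, no dilution of the effect by non-adherence, and power counted on participants with observed outcomes. A baseline correlation of about .53 or more would remove the shortfall at 92. The underlying weakness is that 92 does not follow from the inputs given with it. The amendment sentence matters because it lets the trial shrink towards that figure.

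**What to change.** Either remove the sentence and recruit to the registered 150, or keep it with a floor: the target may be lowered only if the number expected to be analysed at the three-month follow-up (T4) stays at or above the number that gives .80 power for d = .50. That number is 128 unless the test, sidedness and correlation that justify 92 are written down, in which case it is the number they support. If the target is reduced, or already has been, report the power at the actual analysed size in place of .80 (for example, about 66% at 92 on the unadjusted two-sided test).

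This changes one sentence and requires no recruitment beyond 150. The cost is that the trial team loses most of the option to stop recruitment early: with a floor of 128, a reduction is possible only when loss is below about 15%. The change does not itself repair the derivation of 92. At the expected 25% loss, 150 would still give only about 75% on the unadjusted two-sided test.
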